### Participants

People with fibrotic ILD are eligible if they (i) are ≥ 18 years of age; (ii) can provide informed consent; (iii) have been on stable ILD treatment for the month preceding enrolment; (iv) own or have access to a smartphone or tablet to download the REBUILD app to; (v) have access to email; (vi) are able to understand written and spoken English; and (vii) have sufficient digital literacy as quantified by the ability to use a mobile phone, download new apps, and enter keywords into a search box [27]. Exclusion criteria includes (i) acute ILD exacerbation in the month preceding enrolment; (ii) participation in pulmonary rehabilitation at enrolment or; (iii) death or transplant expected within the 12 week intervention period.

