## Statistical considerations

### Sample size justification

A sample size of 400 subjects randomised equally between groups will provide at least 82% power with 95% two-sided confidence to identify a five K-BILD unit improvement from the usual care mean of 55.3 (SD 15.6), with a 5-unit increase considered the minimum clinically important difference [31]. Assuming a pooled SD of 6.5% this offers >95% power to identify a statistically significant difference between groups of 5 points in K-BILD score (change of + 2 in control and + 7 in active arm), allowing for up to 15% of randomly missing endpoint data. Even for a difference of 3 points in Z-score, the study will similarly offer 95% power. This sample size allows for a modest dropout rate of 10%.

Participant mortality should not negatively impact the primary endpoint data as participants expected to die during the 12 week trial period are excluded. Randomisation will be performed using the method of minimisation stratified by (i) FVC: ≤50% or ≥ 51%; (ii) IPF: yes/no; and (iii) treating site.

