### Data analysis

#### Quantitative analysis

The primary endpoint is the difference from baseline in K-BILD scores at 12 weeks according to the intention-to-treat principle. Primary analysis will evaluate whether these differences are larger in the intervention group compared to the control group using 2-sided tests at a 5% level of significance. Key secondary analyses will evaluate the proportion of those with 12-week K-BILD scores above and below 50 and whose K-BILD has increased from baseline by at least 5 units. Additional analyses of secondary endpoints will be performed using standard statistical tests as appropriate.

Associations between 12-week K-BILD score and key baseline variables will be evaluated. Acceptability outcome measures will be reported using the MAUQ. Feasibility will be measured as adherence to the clinical trial (defined as at least 80% completion of data questionnaires). Participants will be considered adherent to the intervention if they receive at least 75% of planned self-management phone calls and access the self-management website on at least one occasion. Percentage of completed modules will also be reviewed, as well as weekly time spent using the app during the study period. The primary and key secondary outcomes will be evaluated in subjects who remain adherent to the intervention in a per protocol analysis.

Analysis of the effect of the REBUILD-SM intervention in key subgroups will also be performed. These subgroups include FVC ≤ 50% or FVC ≥ 51%; IPF yes/no; time since ILD diagnosis < 12 months or ≥ 12 months; and age < 65 or ≥ 65 years.

Modus Research software will be used to retrieve StepWatch data. Participants will be asked to record their activity for 7 consecutive days, and up to 5 complete days of data will be used, with the first and last days of the activity period discarded due to incompleteness. Days with less than 200 steps or less than 24 h of recording time will also be discarded. Average steps per day over all included days will be calculated and difference in measures of physical activity between baseline and week 12 will be compared between groups.

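### The key secondary K-BILD sentence mixes an unexplained week-12 cut of 50 with a 5-unit gain: taken alone the cut is insensitive, and taken jointly it drops some participants who improve

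*Protocol article*

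**What the plan says.** The Quantitative analysis section of the protocol article sets the primary endpoint as change in K-BILD from baseline to 12 weeks. Its key secondary analyses are then described in a single sentence, whose target is this: "proportion of those with 12-week K-BILD scores above and below 50 and whose K-BILD has increased from baseline by at least 5 units". The primary and key secondary outcomes are to be repeated in a per-protocol analysis, so this definition is used twice.

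The sentence does not say whether it describes two analyses or one condition with two parts. The article gives no rationale for 50 and does not mention where participants stand relative to 50 at baseline. The 5-unit gain does have support. The Sample size justification describes the change it regards as clinically important in these words: "with a 5-unit increase considered the minimum clinically important difference". The planning mean and SD come from the same section, which sizes the trial for a "five K-BILD unit improvement from the usual care mean of 55.3 (SD 15.6").

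The eligibility criteria under Participants place no upper or lower limit on K-BILD at entry.

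**The concern.** A cut on the attained score tells the arms apart only through participants whom treatment moves across it. If most are already above 50 at entry, few can cross, and the proportion above 50 at week 12 largely repeats the baseline distribution. On such a cut alone, someone who falls from 70 to 51 ends above it, and someone who rises from 30 to 45, three times the 5-unit threshold, ends below it.

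Two things are at stake. A pre-specified key secondary analysis could have little power under the very effect the trial is planned around. And because the wording allows more than one reading, the reported proportion in the active arm could be about 77–79%, 62% or 51–52%, depending on how the sentence is coded. In a trial with unblinded participants and a self-reported outcome, that choice is better fixed before the data are seen.

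**Working it through.** **Inputs, all from Sample size justification.**
- K-BILD mean 55.3, SD 15.6. The article calls this the usual care mean; using it as the baseline mean is an assumption, as is normality.
- Expected changes: "change of + 2 in control and + 7 in active arm".
- "Assuming a pooled SD of 6.5", printed with a percent sign. I read it as an SD of change of 6.5 K-BILD points, also an assumption.
- "A sample size of 400 subjects randomised equally between groups": 200 per arm, or 170 with the stated 15% missing data.

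**The plan's own figure.** The article states at least 82% power for a 5-unit difference with SD 15.6, two-sided 5%. At 170 per arm, 5 / (15.6 × √(2/170)) = 2.955, and Φ(2.955 − 1.96) = 84.0%. At 200 per arm it is 89.4%, and at 180 (10% loss) 86.0%. The stated figure is met. The article gives no figure for the key secondary analyses.

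**Share above 50 at entry.** 1 − Φ((50 − 55.3)/15.6) = 63.3%. If 55.3 is instead where controls stand at week 12, the baseline mean is 53.3 and the share is 58.4%. Only about 15% start between 43 and 50, within the expected active-arm gain of the cut.

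**Cut taken alone (week 12 above 50).** Two structures were tried.
- Equal variance at both visits (correlation 1 − 6.5²/(2 × 15.6²) = 0.913): control Φ(7.3/15.6) = 68.0%, active Φ(12.3/15.6) = 78.5%.
- Change independent of baseline (week-12 SD √(15.6² + 6.5²) = 16.9): control Φ(7.3/16.9) = 66.7%, active Φ(12.3/16.9) = 76.7%.

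**Gain of at least 5.** Control 1 − Φ((5 − 2)/6.5) = 32.2%; active 1 − Φ((5 − 7)/6.5) = 62.1%.

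**Joint criterion (above 50 and gain of at least 5).** Simulated, 4 million draws per arm.

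| Reading | Control | Active | Contrast | Power at 200 / 170 per arm |
|---|---|---|---|---|
| Cut alone | 67–68% | 77–79% | about 10 points | 60–66% / 53–59% |
| Gain of at least 5 | 32% | 62% | about 30 points | above 99.9% |
| Joint | 24.5–26.4% | 51.1–52.4% | 26–27 points | above 99% |

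**What the cut alone counts.** In the same simulations, 87–88% of controls and 83–84% of active participants stay on their baseline side of 50. Of those above 50 at week 12, 87–88% (control) and 79–81% (active) were already above it at entry.

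**What the joint reading misses.** Of those who gain at least 5 units, 18–24% (control) and 16–18% (active) end at or below 50. With a baseline mean of 53.3 these become 28% and 21%.

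**Sensitivity.** With baseline 53.3, the cut alone gives 63.3% v 74.6%, an 11-point contrast with power 61–68%. With an SD of change of 10 (equal variance), the gain criterion gives 38.2% v 57.9%, about 20 points, with power 96–98%; the cut alone stays near 10 points with power 59–66%.

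**If the cut is kept.**
- Adjusting for baseline score in a logistic model of all participants gives power of about 90–95% at an SD of change of 6.5. A rerun with an SD of 10 gave roughly 75–87%.
- As a transition among those at or below 50 at entry (about 37%, or 0.367 × 200 = 73 per arm), crossing rates with equal variance are 0.0878/0.367 = 24% and 0.1623/0.367 = 44%, with power about 73%. With an SD of 10 they are 0.1207/0.367 = 33% and 0.1835/0.367 = 50%, with power about 56%, below the 66% of the unadjusted cut in all 200 per arm.

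**The case against.** The strongest objection is that the sentence already contains the 5-unit gain. Read as separate analyses, the stand-alone gain responder is planned, it counts the 30-to-45 improver and not the 70-to-51 decliner, and the cut is only a less sensitive companion. Read jointly, nobody who declines can be counted and the contrast is nearly that of the gain alone. This stands. A reader might infer that the endpoint as a whole mainly counts baseline status, credits decliners and hides the treatment effect. The documents do not support that: those harms belong to the cut taken alone, while the missed improvers belong to the joint reading, and no single reading has both.

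It can also be said that attained state and change answer different questions, that the article never calls 50 success or failure, and that randomisation balances baseline status on average. This stands too: the cut costs sensitivity and does not bias the comparison between arms.

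A full protocol or SAP may give the reason for 50, the handling of a score of exactly 50 and the coding. Their absence from an article is not itself a fault. But the article does fix the cut of 50 within its key secondary analyses, and its low sensitivity follows from the article's own planning figures.

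Finally, 55.3 is not labelled a baseline mean and the 6.5 is printed as a percentage. Both are assumptions here. That most participants start above 50 survives the range tried, 58–63%.

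**Conclusion.** The point holds as a cheap improvement to a key secondary analysis, not as an error that threatens the trial's conclusions. Under either reading the cut of 50 adds little and costs something. Alone, it shrinks the expected contrast from about 30 points to about 10 and the power from above 99% to about 53–66%. Jointly, power stays above 99%, but about 16–24% of participants who gain the protocol's own minimum important difference are left out because they end at or below 50.

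These sizes rest on normal scores, 55.3 (SD 15.6) standing for baseline, an SD of change of 6.5 points, and changes of +2 and +7. With an SD of change of 10 the advantage of the gain criterion is smaller but still clear (about 20 points against 10). The primary endpoint, a continuous change from baseline, is unaffected.

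**What to change.** State that the key secondary responder endpoint is a K-BILD gain of at least 5 units from baseline at week 12, standing alone, and that it is not combined with any absolute score.

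Either drop the 50 cut or keep it as a separate exploratory analysis, with a score of exactly 50 assigned to one side and baseline K-BILD accounted for. Adjusting for baseline score in all participants is the more efficient choice. A transition analysis among those below 50 at baseline is easier to explain, but it uses only about 37% of participants and gains little or no power if the SD of change is nearer 10.

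The cost is a change of wording in the analysis section and in any SAP. No new data are needed. Enrolment is expected to continue to December 2026, so the wording can be settled before any unblinded analysis.

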### Intervention – self-management package

In addition to standard care, the intervention group will receive access to the ILD self-management content, four health coaching support phone calls, and the full version of the REBUILD app including educational resources. While the intervention is designed to improve the ability of participants to self-manage their disease, it is not intended to replace clinical care for either group. Both groups still attend their regular ILD clinic reviews and are managed according to usual care pathways by their treating team.

The intervention group can access the self-management package via *pflivingwell.com* and the REBUILD app (Fig. 1). The content includes 13 modules, organised by topic, each providing key information and embedded hyperlinks to relevant website, factsheet, booklet, video, and webinar resources vetted by our research team. The intervention is designed to improve self-management through information and activities related to goal setting, symptom tracking, self-reflection and problem-solving, compared with self-monitoring through the app alone [22]. Prior to accessing the self-management content, the intervention group complete an online introduction to identify which modules best align with their personal concerns and goals. Participants are then encouraged to review these modules throughout the intervention period.

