### Health coaching support calls

The intervention group will receive health coaching via phone or video call at 4 time points (week 1, 2, 3 and once between week 6 and 12) during the study period, with the aim of promoting engagement with the self-management modules. Calls will be made by an ILD healthcare professional who, throughout the intervention period, may provide support such as (i) guidance in identifying appropriate modules; (ii) assisting the participant to set health-related goals and identify strategies to achieve these; (iii) monitoring progress; (iv) addressing challenges; and (v) providing feedback or clinical recommendations. These calls also provide an opportunity for the healthcare professional to assess the participants’ understanding and tailor support accordingly. The outcomes of each session will be documented.

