#### Your diaries

Participants can record their medications, side effects, and supplemental oxygen use here and are encouraged to keep this information updated. The intervention group can also access the self-management content here.

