### Aims and outcomes

This study aims to compare the clinical efficacy and cost-effectiveness of the self-management package delivered through the REBUILD app to standard clinical care; and to understand the barriers and facilitators to adoption of the intervention. The study team hypothesise that REBUILD-SM will (1) improve HRQoL, symptoms, anxiety, self-efficacy, and physical activity in people with ILD; (2) be a cost-effective intervention compared to standard care; and (3) be implementable in clinical practice.

The primary outcome is change in HRQoL measured by change in King’s Brief Interstitial Lung Disease (K-BILD) questionnaire score at 12 weeks. The K-BILD has been chosen as a valid, ILD-specific measure of HRQoL with demonstrated responsiveness to interventions; [31] and this timepoint was selected based on evidence showing change in physiological variables at 12 weeks to be predictive of mortality and disease progression in IPF patients [32]. Pulmonary rehabilitation (commonly lasting between 8 and 12 weeks) has also demonstrated efficacy in improving short-term HRQoL in people with IPF, [33] suggesting that 12 weeks will be sufficient to observe a treatment effect.

The secondary outcomes are as follows (see also Table 1):

Change in K-BILD score from baseline at week 26 and 52; and change in EQ-5D-5L score from baseline at week 12, 26 and 52Change in General Self-Efficacy Scale (GSE) score from baseline at week 12, 26 and 52Change in Dyspnoea-12 score from baseline at week 12, 26 and 52Change in Hospital Anxiety and Depression Scale (HADS) score from baseline at week 12, 26 and 52Change in physical activity level from baseline at week 12 and 52Uptake or changes to ILD treatments, including clinical trial enrolment at week 12, 26 and 52Acceptability of the REBUILD app, evaluated utilising the mHealth App Usability Questionnaire (MAUQ) score at week 12, 26, and 52; and app analytics, including frequency the app and its individual features are accessed and used, total time of use and percentage of complete data enteredChange in eHealth and Literacy Scale (eHEALS) score from baseline at week 12 and 52Autonomy, which will be evaluated using the Healthcare Climate Questionnaire (HCCQ) at week 12

**Table 1 Tab1:** Study endpoints

**Data collection**	**Baseline**	**Week**			
		**12**	**26**	**38**	**52**
Demographic and clinical information	**X**		**X**		**X**
HRQoL (K-BILD & EQ-5D-5L questionnaire)	**X**	**X**	**X**		**X**

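### The per-protocol adherence rule counts only website access, although the plan also delivers the same self-management content inside the REBUILD app

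*Protocol article*

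**What the plan says.** The rule is in the protocol article under Quantitative analysis. It has two parts joined by 'and'. To count as adherent, the participant must "receive at least 75% of planned self-management phone calls and access the self-management website on at least one occasion". The same paragraph says that the primary and key secondary outcomes will be analysed per protocol in those who stay adherent. The primary analysis itself follows intention to treat.

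The delivery of the content is described elsewhere:

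- Intervention – self-management package: "The intervention group can access the self-management package via *pflivingwell.com* and the REBUILD app".
- Your diaries, a section of the app: "The intervention group can also access the self-management content here".
- Aims and outcomes: the trial evaluates the "self-management package delivered through the REBUILD app".

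The percentage of modules completed and the weekly time in the app are to be reviewed as well, but they are not part of the adherence rule.

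**The concern.** A per-protocol set should separate participants by how much of the intervention they took up. This rule can separate them by the route they used. The route it leaves out is the one named in the trial's aim, and participants already use the app for consent, randomisation and questionnaires, so use of the modules only in the app is foreseeable.

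Two things are at stake. Reported adherence could be too low. The per-protocol estimate could also be biased, because people who work only in the app may differ from those who use the website, for example in age or digital confidence. Some loss of precision would follow too, but selection is the more serious matter.

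**Working it through.** **1. The call part.** Four coaching calls are planned (Health coaching support calls). At least 75% of 4 is 0.75 × 4 = 3, so 3 or 4 calls meet this part. Table 2 uses a stricter limit, more than 75%, for a separate implementation measure; nothing here depends on it.

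**2. The rule applied literally to four hypothetical participants.**

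| Calls received | Website visits | Modules opened in app | Status under the rule |
|---|---|---|---|
| 4 of 4 | 0 | all 13 | non-adherent |
| 3 of 4 | 1 | none | adherent |
| 2 of 4 | 1 | none | non-adherent |
| 2 of 4 | 0 | all 13 | non-adherent |

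The first two rows show the problem: the participant with more calls and full use of the content is left out, and the one with a single website visit is kept. The third row shows that a website visit is not enough by itself. The fourth shows that app-only users who miss the call threshold are non-adherent in any case, so the rule misplaces only app-only users with at least 3 calls.

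**3. Consistency with other measures.** Table 2 (Adoption) counts uptake by access to the app on at least one occasion. The same person can therefore count as having taken up the intervention and as not adherent to it.

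**4. Size.** The article gives no split by route, so no count can be derived. The effect on precision can only be illustrated under assumptions: two-sided 5% test, normal approximation, a difference of 5 points, and 170 evaluable per arm (200 × 0.85, from the 15% missing data allowed for). A share s of the intervention arm is removed, everyone is taken to meet the call threshold, and the control arm is kept whole.

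Power = Φ( 5 / (SD × √(1/n₁ + 1/n₂)) − 1.96 )

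Starting from the plan's own figure: with SD 15.6, 200 per arm gives 89.3% and 170 per arm gives 84.0%. Both are consistent with the stated minimum of 82%. Then, with n₂ = 170 and SD 15.6:

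| Assumed app-only share s | n₁ | Per-protocol power |
|---|---|---|
| 0% | 170 | 84.0% |
| 10% | 153 | 82.0% |
| 20% | 136 | 79.6% |
| 30% | 119 | 76.5% |
| 50% | 85 | 67.5% |

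Worked line for 20%: √(1/136 + 1/170) = 0.1150; 15.6 × 0.1150 = 1.795; 5/1.795 = 2.786; Φ(2.786 − 1.96) = 79.6%. With the article's other SD, 6.5, power stays above 99% across the whole range. The loss of precision therefore depends on an unknown share and on which SD applies. The selection problem does not depend on the SD.

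**The case against.** The strongest reply is that the app may simply open the website. Participants first "complete an online introduction to identify which modules best align with their personal concerns and goals"; if that step sits on the website, everyone who reaches the content has already met the rule. The Control group section also treats the package as separable from the full app, since controls receive the full app at week 26 without the package. That fits content hosted on the web. This part of the reply stands: the article does not settle how access is logged, and misclassification is not certain. It does not remove the point, because the article names two routes and its rule counts one, without saying that an in-app opening registers as a website visit.

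A second reply is that logging detail belongs in the full protocol or the analysis plan. That would hold if the article were silent. It states an explicit rule, and the rule does not match its own account of delivery.

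A reader might also fault the two descriptive measures: module completion, if it is counted out of all 13 modules in a tailored package, and app time, because it misses website use. The documents do not support this. No denominator is given for module completion, Table 2 counts modules accessed without naming a route, and neither measure decides who enters the per-protocol set.

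**Conclusion.** The point holds as a mismatch between a stated rule and the plan's own description of delivery. Followed literally, the rule leaves out of the per-protocol analysis any intervention participant who meets the call threshold but uses the modules only in the app. This rests on one assumption that the article neither confirms nor excludes: that in-app openings are not logged as website visits.

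The number affected is unknown; the shares in the power table are illustrations, not estimates. Three stronger readings are tempting and are not supported:

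- That the primary result is at risk. It is analysed by intention to treat and does not use this rule.
- That a website visit alone makes a participant adherent. At least 3 calls are also needed.
- That a sizeable group will certainly be misclassified. No document gives the share of app-only users.

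The correction is worth making because it costs little and makes the per-protocol set reflect use of the content.

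**What to change.** Keep the call threshold. Replace the content part of the rule with: opened at least one self-management module by either route (website or REBUILD app) before the week-12 K-BILD. Derive it from the website and app logs combined.

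Two features of this wording matter. It asks for a module, because every participant opens the app to consent and merely opening it would show nothing about exposure. It sets a time limit, because the present rule states none and would accept a first visit made after the primary endpoint.

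If in-app openings already register as website visits, say so in the rule; no app-only user would then be misplaced.

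The cost is a wording change and a merge of two usage logs. App analytics and counts of modules accessed are already planned (Aims and outcomes; Table 2). The small downside is linking website log-ins to study IDs. The change should be fixed in writing before outcome data are examined by arm.
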